## Abstract

**Background:**

Globally, cancer rates are increasing. In Scotland, it is estimated that 2 in 5 people will develop cancer in their lifetime. Therefore, this is crucial time to provide personalised care and support to individuals affected by cancer. In response to this a community based supportive cancer service was launched in Glasgow, Scotland. The aim of this service is to proactively provide those affected by cancer with an assessment of their needs and personalised support where needed. To our knowledge, there is no other service like this in the United Kingdom.

**Methods:**

The aim of this study is to understand if and how the service impacts upon the experiences and outcomes of people living with and affected by cancer. The study uses a sequential mixed methods design across a 5 year time point. Data gathering includes questionnaires, interviews, observations and reflective diaries. Participants include people affected by cancer who have used the service, a comparative sample who have not used the service, individuals who deliver the service and wider stakeholders. Outcomes include measures of patient activation, quality of life, health status, and social support. Data collection occurs at baseline, 2.5 years and 4 years with data from observations and reflective diaries supplemented throughout.

**Discussion:**

This study evaluates an innovative community based cancer service. It focuses on impact and process issues relevant to a) the individuals in receipt of the service, b) the service providers, and c) the wider culture. As the programme evolves overtime, the research has been designed to draw out learning from the programme in order to support future commissioning both within Scotland and across the UK.

## Background

Globally cancer is a leading cause of death. The World Health Organisation (WHO) estimated there were 14.1 million new cases of cancer in 2012, predicting this figure will rise by a further 20 % to 22 million within the next 20 years [1]. International and national figures show specific and consistent trends in terms of the increasing incidence, prevalence, and survival rates for people with cancer [2]. An ageing population, socio-economic factors and the adoption of lifestyle behaviours such as smoking, drinking alcohol, poor diet and physical inactivity all contribute to the increase of cancer cases [3].

In the United Kingdom (UK), cancer incidence rates have increased by more than a quarter over the last 40 years [2]. Prevalence of different risk factors varies by region and country. In particular, in Scotland cancer survival rates are low in comparison to the rest of Western Europe. This has been partly attributed to the late presentation of cancer and the high rates of lung cancer [4, 5]. Every year, approximately 30,000 people are told they have cancer in Scotland [6]. The predicted increase in the incidence of new cases of cancer in Scotland will be 33 % over the next 15 years resulting in over 40, 000 new cases per year between by the years 2023–2027 [7].

Risk factors relating to socio-economic factors and smoking have particular relevance for the Scottish city Glasgow. Glasgow is the biggest city in Scotland and the third biggest in the UK. The link between socio-economic factors, poor health and incidences of cancer are pertinent for the city. Deprivation figures show that Glasgow has 49 % of its total neighbourhoods categorised within the first and second most deprived quintiles [8]. Mortality rates have been found to be significantly higher (30 %) than the rate for other equally deprived cities in the UK such as Liverpool and Manchester [9]. With these factors in mind it was a priority to situate a new cancer initiative within the communities of Glasgow.

Individuals affected by cancer commonly experience some form of burden and distress [10]. Furthermore, a diagnosis of cancer not only impacts the person who is diagnosed but those close to them too [11]. Recognition of the need to screen for distress and provide personalised support services has grown and is a feature of current international policy and clinical practice guidelines [12–14]. Health policy within both the UK and Scotland has moved its emphasis from disease based only models to a person centred approach [15, 16]. Policy recommendations centre on supporting individual needs with the aim of acknowledging not only physical but also social and emotional needs. A number of key values; empowerment, inclusion, joint decision making and holistic needs assessment are enshrined within the definition of personalised care planning [17].

However, despite these evidence based guidelines screening is not always routinely carried out or monitored [14, 18]. Subsequently, there is a large body of evidence reporting unmet needs in those affected by cancer relating to physical, psychological, practical and/or social factors [19–21]. What is more, it has been suggested that the majority of unmet needs are beyond the function of services that are primarily designed to focus on the medical aspects of care [22]. It is against this backdrop that a community based cancer service in Glasgow called ‘Improving the Cancer Journey’ (ICJ) was developed.

‘Improving the Cancer Journey’ (ICJ) is led by by Glasgow City Council (the legislative body that governs the city) and the main partner in funding and support is a UK charity called Macmillan Cancer Support. Other partners include the National Health Service (NHS) and a range of organisations operating in health and social care. The service sends individuals who are newly diagnosed or have had a disease reoccurrence a letter of invitation. This letter invites them to have a Holistic Needs Assessment (HNA) with a named link officer. This is offered in a community setting, such as a local library or the individuals home rather than a clinical setting where a HNA is traditionally carried out. However, individuals can also be referred into the service by their health professional or they can self-refer.

Holistic needs assessment is a common method of screening for distress in cancer care [23]. It is defined as follows:*“Holistic needs assessment is a process of gathering and discussing information with the patient and/or carer/supporter in order to develop an understanding of what the person living with and beyond cancer knows, understands and needs. This holistic assessment is focused on the whole person, their entire well-being is discussed – physical, emotional, spiritual, mental, social, and environmental. The process culminates when the assessment results are used to inform a care plan.”* [24]

The assessment allows the link officer to understand what the central concerns are for that individual (Fig. 1). The individual completing the assessment is asked to consider on a scale of 1–10 how much the issue identified is causing them concern. This allows the service to identify if an individual’s level of concern changes over time. The link officer is a member of staff employed by Glasgow City Council with a background in either housing and/or social care. The service also has a seconded Cancer Nurse Specialist who provides clinical support to the team, a patient reference group and a clinical psychologist who provides supervision for the link officers.

**Fig. 1 Fig1:**
[figure not shown]
Holistic Needs Assessment- The Concerns Checklist

Through administering a HNA the link officer can devise an individualised care plan and provide guidance and support to the person affected by cancer in order to access local services in relation to their needs. The link officer revisits each case approximately every 4 to 6 weeks, (or sooner depending on need) closing the case when they agree with their client that they require no further assistance from the service. The service also offers support to carers. For the purposes of this research a ‘carer’ refers to anyone who cares unpaid for the person with a cancer diagnosis. For example, this may be their spouse, friend or next of kin.

Improving the Cancer Journey (ICJ) was launched in February 2014 with a pilot phase focusing on five cancer groups. This service was then extended to all cancer types. It has been commissioned for 5 years. As of July 2016 the service has supported 1801 people. 52 % are female and 48 % are male. It supports most people in the 50–64 age bracket and 93 % of those who have accessed the service identify as having a white ethnicity. The most common primary diagnosis is lung cancer, followed by breast cancer.

This research was commissioned to focus on *impact* and *process* issues relevant to a) the individuals in receipt of the service, b) the service providers, and c) the wider culture. This research runs alongside the life of the programme for the next 5 years and is designed to draw out learning from the programme in an ongoing way.

### Aim and objectives

The overarching aim of this study is to understand if and how ICJ impacts upon the experiences of people living with and affected by cancer. There are 2 objectives:To identify the impact of ICJ on those diagnosed with cancerTo understand the process of ICJ as experienced by○ Patients and carers in receipt of the service○ The service providers, and○ The wider culture.

Hypotheses are:Individuals who have engaged with ICJ will report significantly different mean scores on patient activation measures than those who have not.Individuals who have engaged with ICJ will report significantly different mean scores on quality of life measures than those who have not.Individuals who have engaged with ICJ will report significantly different mean scores on social support than those who have not.Self -reported experience of ICJ will be significantly associated with scores on quality of life measures, patient activation scores and support.

## Design/Methods

This study uses a sequential mixed methods design. The main rationale for using mixed method research is triangulation of the data.

### Data

This study will incorporate the following data gathering methods across the 5 years:

#### Quantitative data

Validated questionnaires (PAM-13, FACT-G, EQ5D-3L, MOS-SSS), analysis of routinely collected service data and self-reported experience of ICJ. See ‘Measures’ below for detail.

#### Qualitative data

Free textInterviews with patients and carersReflective diaries for the link officersObservation of the link officers.

### Intervention

Holistic needs assessment and targeted support. A link officer conducts a holistic needs assessment (HNA) with a person affected by cancer. A care plan is then co-constructed between the worker and the person. Actions from the care plan may include referral to an external agency, referral back to the health service, signposting to another service or providing self-management information. The care plan is revisited at each meeting between the link officer and the person affected by cancer until issues are resolved.

### Eligibility criteria

#### Patients and carers who have used ICJ

For inclusion in this research the patient and/or carer will have received the intervention.

Inclusion criteria:Over 24 years old (this is a requirement of the ICJ service)Live in GlasgowDiagnosed with cancer or supporting someone with a cancer diagnosisHad a HNA with a link worker as part of the ICJ service

Exclusion criteria:Professional carer (eg paid to provide care)Person deemed incapable of consenting to participate as defined by the Adults with Incapacity Act (2000)Any reason which in the opinion of the clinician/investigator interferes with the ability of the patient to participate in the study

#### Patients who have been offered but not received ICJ

This study will also include data from a sample of individuals diagnosed with cancer that have been offered ICJ but not taken up the offer (for any reason). The reason for including this non ICJ sample is to a) understand why people have not taken up the service and b) to compare activation, quality of life, health status and support levels according to whether people had received ICJ or not.

#### Link officers

There are currently 7 link officer employed full-time by this service. All will be included in the study unless they choose not to participate.

#### Other stakeholders

There is a range of partners involved in this service as described in the background section. In addition, there are various agencies and services that the patients and carers may engage with as a function of this service, such as psychological services and third sector organisations. These stakeholders will be invited to participate in annual workshops.

### Measures

Participants who have used ICJ and the comparable sample of participants who have been offered but not received ICJ will receive a postal questionnaire. The questionnaire contains validated measures of patient activation, quality of life, health status, social support, a free text box and space to prove contact details if they wish to take part in qualitative follow-up interviews.

#### Patient activation

Patient activation is a behavioural concept relating to an individual’s self-management needs, abilities and priorities. The patient activation measure short form (PAM-13) is a 13-item Likert measure constructed to identify different levels of patient activation. These levels have been used to estimate costs in relation to service use such as hospital admissions and accident and emergency usage [25]. A related benefit of this measure is that the levels are a useful indicator of the types of support individuals may require form health professionals to engage in self-management [26].

#### Quality of life

Participants will complete the functional assessment of cancer therapy-general (FACT- G) and the EQ-5D [27]. FACT-G is a validated measure of quality of life in a general cancer population [28, 29]. EQ-5D is a standardised instrument for measuring economic preferences for health states. It is in widespread use in many countries and provides a simple descriptive profile and index value for health status [30].

#### Social support

The Medical Outcomes Study Social Support Survey (MOS SSS) is a validated measure of perceived social support that was developed for patients with chronic conditions [31]. It encompasses several domains of support including tangible support, emotional support and positive support.

#### Open-ended question

At the end of the questionnaire a separate free-text box asks ‘If you have anything else you would like to tell us about living with cancer please do so here’. The aim is to analyse the content for any themes relating to individuals cancer experiences.

#### Self-reported experience of ICJ

The service sends every individual an evaluation questionnaire following their final visit. It asks a mixture of closed and open-ended questions relating to their motives for taking up the service, their experiences with the link officer and what impact the service may have had in terms of reducing concerns and fostering self-management. Where available this data will be matched up with the data from our questionnaire to examine if there are any associations between self-reported experience of ICJ and patient activation, quality of life and social support.

### Recruitment

#### Individuals who have used ICJ

At the initial meeting where the HNA takes place individuals are asked for their consent to share their data. For those who have consented ICJ keep a record of contact details for all their clients. All individuals who meet the inclusion criteria will be invited to participate. Participants will receive a study pack through the post. This will contain a welcome letter, participant information sheet, consent form and questionnaire booklet. If they wish to take part they will be provided with a stamped addressed envelope to return the questionnaire and consent form.

A final question on the questionnaire asks if they wish to take part in follow up interviews with a researcher. If they do, they will be asked to provide their contact details so the researcher can arrange this. The research team will recruit patients and carers this way. In year one the target is to interview 20 patients and carers who have used ICJ and indicated on the questionnaire that they wish to take part. We will purposively seek to recruit consenting participants who have experienced a wide range of outcomes as evidenced in their questionnaire responses. We will target different cancers and cancer stages to help obtain a broad sample. Written informed consent will be obtained for all interview participants. The process will be repeated at 2.5 and 4 years.

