#### Individuals who have been offered but not received ICJ

A stratified sample based on gender, age, cancer type and socio-demographic band will be developed based on the ‘individuals who have used ICJ’ sample. The service will also post the study pack on behalf of the research team to this sample alongside a reminder that ICJ is still available to them should they so wish.

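### Interviewees are to be selected on cancer stage, but no source for stage is named, and both the comparator sampling and the unadjusted comparison of users with decliners leave it out

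*Protocol article*

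**What the plan says.** All references are to the Protocol article.

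- **Interview selection** (Recruitment, Individuals who have used ICJ). The year-one aim is stated as "In year one the target is to interview 20 patients and carers who have used ICJ". Selection is purposive. It seeks "participants who have experienced a wide range of outcomes as evidenced in their questionnaire responses", and adds: "We will target different cancers and cancer stages to help obtain a broad sample".
- **Questionnaire** (Measures). Both groups receive the same postal booklet: "The questionnaire contains validated measures of patient activation, quality of life, health status, social support, a free text box", plus space for contact details. Neither stage nor extent of disease is in the list.
- **Comparator sampling** (Recruitment, Individuals who have been offered but not received ICJ). "A stratified sample based on gender, age, cancer type and socio-demographic band will be developed", taking the user sample as its template.
- **Service data.** The Quantitative data section also lists "analysis of routinely collected service data and self-reported experience of ICJ", without naming the fields. For users, the consent route is stated: "At the initial meeting where the HNA takes place individuals are asked for their consent to share their data". The Background, after Fig. 1, describes clients by sex, age, ethnicity and diagnosis ("The most common primary diagnosis is lung cancer, followed by breast cancer").
- **Analysis** (text under Power analysis). Mean scores on PAM-13, FACT-G, EQ-5D and the MOS survey are compared between groups by t-test, or by a corresponding nonparametric method if assumptions fail. No covariate is named.
- **Discussion.** The comparator is called matched. Living in the same city is said to limit confounding, with a different health board as the example. Stage is not mentioned.

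**The concern.** Stage is used to give breadth to about 20 qualitative interviews, but not in the quantitative comparison that tests Hypotheses 1 to 3, where it could do most harm. Extent of disease plausibly affects FACT-G and EQ-5D scores directly. It may also affect whether a person accepts an offer of support. The Background says that invitations go both to newly diagnosed people and to people whose disease has returned, so extent of disease can vary widely within one cancer type. Two people with lung cancer of the same age, sex and deprivation band may have very different disease.

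If users and decliners differ in stage after stratification, the t-test attributes that difference to ICJ. The bias could hide a real benefit if users are the sicker group, or create an apparent one if decliners are. A larger sample would not remove it. If stage is neither in the records nor in the booklet when the survey is posted, adjusting later would require going back to participants or records.

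**Working it through.** **Step 1. Where stage could come from**

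| Place in the article | What it lists | Stage? |
|---|---|---|
| Interview selection | cancers, stages, range of outcomes | yes, as a criterion |
| Questionnaire content | validated scales, free text, contact details | not listed |
| Comparator stratifiers | gender, age, cancer type, socio-demographic band | not included |
| Description of clients | sex, age, ethnicity, primary diagnosis | not mentioned |
| Routine service data | fields not itemised | unknown |
| Group comparison | t-test or nonparametric equivalent, no covariate | not included |

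The stratifiers and the test are positive statements of method, and both leave stage out. The source of stage is a different matter: it is simply not named.

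**Step 2. The plan's own sample size**

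Inputs from the Power analysis section: d = 0.5, alpha = 0.0167, power 95%. A two-sided two-sample t-test by the noncentral t gives 131.9, so 132 per group and 264 in total. Power at 132 per group is 0.950. The stated figure reproduces, and no error is claimed in it.

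**Step 3. What an imbalance in stage would do**

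The article gives neither input, so both are assumptions:

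- difference between groups in prevalence of advanced disease, remaining after stratification: 10 to 20 percentage points;
- difference in mean score between advanced and other disease: 0.5 to 0.8 SD.

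Shift in the group difference = prevalence difference × score difference.

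Noncentrality = shift / √(2/132) = shift / 0.1231, with 262 degrees of freedom and two-sided alpha 0.0167.

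| Prevalence difference | Score difference | Shift (SD) | Rejection rate with no true effect |
|---|---|---|---|
| none | any | 0 | 0.0167 |
| 0.10 | 0.5 | 0.05 | 0.026 |
| 0.10 | 0.8 | 0.08 | 0.042 |
| 0.20 | 0.5 | 0.10 | 0.057 |
| 0.20 | 0.8 | 0.16 | 0.136 |

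The rejection rates are two-sided, so they are the same whichever group is sicker.

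If users are the sicker group and the true effect is d = 0.5, the observed difference is centred on:

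- 0.5 − 0.05 = 0.45, power 0.893;
- 0.5 − 0.16 = 0.34, power 0.638.

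If decliners are the sicker group, the shift goes the other way and inflates the apparent benefit.

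**The case against.** The strongest reply is that much of this argues from silence in a condensed article.

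- **Service data.** They are a listed source with unstated fields, and the client description in the Background is not a data dictionary. Socio-demographic band shows this: it is a stratifier but is absent from that description. This stands.
- **Interviews.** A reader might infer that selection by stage cannot be carried out. The article does not support that. Interviewees are users who are asked to consent to data sharing and who give contact details, so stage could come from records or be asked when the interview is arranged. The criterion is also a loose aim for breadth, not a quota.
- **Decliners.** A reader might infer that nothing is known about their disease. That is too strong as well. To stratify them by cancer type, the service must hold some record of them. They have had no HNA, however, so the assessment and its consent step do not exist for them.
- **The booklet.** A background page may have been left out of the article. The absence of a stage item is therefore not proved.
- **Treatment status.** It is not an interview criterion in the article, and its absence breaks no stated rule.
- **The general weakness.** The Discussion concedes that reasons for declining are unknown and that decliners may already be well supported. It promises to explore those reasons and give descriptive statistics. This covers part of the selection problem, but it does not mention stage and does not change the test.

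The reply does not remove the point about method. The stratifiers and the comparison are stated, stage is in neither, and the comparator is still called matched. Covariates may be left to an analysis plan, but the test named here has none.

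**Conclusion.** The point holds in a limited form. The article selects interviewees on stage without naming a source for it. As written, the comparison of users with decliners neither stratifies on stage nor adjusts for it, so differences in FACT-G and EQ-5D can be confounded by stage within cancer type. The consequence is greatest for decliners and for the quantitative comparison, and slight for the interviews.

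The range of 0.05 to 0.16 SD shows what an imbalance could do. It is not evidence that one exists. It rests on an assumed prevalence difference that survives stratification, an assumed effect of stage on the scores, and an unknown direction. This is a worthwhile and inexpensive improvement to the comparison. It does not show that the study cannot be carried out.

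**What to change.** 1. State where stage comes from for users and for decliners.
2. Unless service records already supply it for both groups, add one self-reported item on extent of disease to the common questionnaire (localised / spread / don't know). An item on treatment status is optional.
3. Tabulate the item by group, with don't-know and missing answers shown.
4. Replace the unadjusted comparison with a regression of each score on group, adjusting for extent of disease, gender, age, cancer type and socio-demographic band.
5. In the Discussion, say which variables the comparator is matched on, and name stage as a possible confounder.

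The cost is one or two tick-box questions, an ethics notification and a slightly longer form. Self-reported extent will contain error and some don't-know answers, so adjustment will reduce confounding by stage but not remove it. If the booklet or the service records already hold the item, only the statement of source, the table, the adjusted analysis and the Discussion wording are needed.
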